## Background

Longitudinal cohort studies are essential in understanding the etiological mechanisms of underlying hypotheses. It is particularly challenging to develop and sustain birth cohorts, as the observation period spans several years making it vulnerable to lose tracking subjects for several reasons. These include a change in the location of residence, lack of interest in the study, death etc. [1, 2]. Few groups are at higher risk of selective attrition, particularly ethnic minorities, those with low family income or low education, and those living in urban areas [3].

The results from prospective cohort studies can be unbiased, only if they can maintain greater compliance of follow-up. The loss to follow-up can result in biased estimates [4], if the reason for the loss is related to the outcome of the investigation. The cohort studies done in India have variable rates of loss to follow-up ranging from 14 to 82% [1, 2, 5, 6]. Continuous follow-up and ensuring retention of participants is challenging due to many reasons. These include lack of trust in the research, concerns about research design, the consent process, discordance between lay beliefs, medical practice and cost of travel, etc. This challenge is intricate given that pregnant women accessing public health facilities do not turn up for regular antenatal health checkups [7]; which are influenced by limited decision making power regarding their health, poor access, transport for routine care, perceived the poor quality of health care facilities and limited staff/financial constraints [8]. According to the National Family Health Survey (NFHS) (2014–15), only 55.5% of women in urban Bengaluru had the required four antenatal care visits during pregnancy [9].

Some reviews have reported different strategies like using a mobile phone, Interactive voice response, antenatal sessions and community-centered approaches for improving study participation and retaining a greater proportion of participants [10–17]. For example, an automated voice call was used to improve adherence to iron supplementation during pregnancy [10]. However, little is known about the effectiveness of specific retention strategies deployed in retention of mothers and infants in a birth cohort.

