MAASTHI is a prospective birth cohort with the aim of assessing the effects of glucose levels in pregnancy on the risk of adverse infant outcomes, especially in predicting the possible risk markers of later chronic diseases [18]. The recruitment of the pregnant women in MAASTHI began in April 2016. The current strategy deployed in MAASTHI cohort is to follow up pregnant women for Oral Glucose Tolerance Test (OGTT), at birth and in-person child assessments at 14 weeks, annually during the year 1, 2 and 3 of the child. Currently, we are recruiting around 80 pregnant women per month, with the completion of all their records, anthropometry measurements, and OGTT. Of the eligible pregnant women, only 77% completed OGTT despite offering the test free of cost and repeated reminders by the research team to get tested for gestational diabetes. Once the OGTT is done between 24 and 36 weeks of gestation, there is no further opportunity to meet them again until the delivery. The duration without contact increases the likelihood of attrition. In the intervening period of initial contact and follow-up’s, it is essential that the participants are continuously engaged by the research staff through innovative methods in order to attain better turn up rate for follow up. Despite stringent adherence of including only the residents of the source population, nearly 20% of the women did not attend the follow-up visits at birth. In order to prevent further loss to follow-ups in subsequent visits, we are interested in exploring whether interventions involving Interactive voice response system (IVRS) and conducting mother and baby workshops can improve follow-up rates.

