### Implementation

The research staff will inform the study participants of MAASTHI birth cohort regarding the interventional trial. Upon voluntary informed consent, the research staff will screen the participants for eligibility and will randomly allocate to one of the study arms. Necessary demographic details, socioeconomic status, diet, physical activity are recorded. Participants will be randomly allocated to the study arms-, IVRS arm, MBA arm or control arm. They are invited to undergo the OGTT between 24 to 36 weeks of gestation. A portion of the blood sample will be stored at − 80 degrees for future biochemical and genetic tests.

In addition to the standard care, the MBA arm will receive intervention in the form of awareness workshop from specialist doctors. There will be role plays and quizzes, participants who win will receive small gifts from the study team.

Along with standard care, the IVRS intervention involves calls to pregnant women at specified periodic time intervals providing them with antenatal care tips, and reminder calls for OGTT and follow-up visits to the hospital. They are also given the opportunity to identify any issues or concerns that they may have with IVRS. Through IVRS, participants will be informed that the IVRS supplements, but do not replace, existing clinical services and that all emergencies should be handled by usual means. If the respondent does not wish to continue in the IVRS arm, they will have the option to move out of this arm and continue in the control arm.

The participants in the control group receive standard care; they will be explained the importance of glucose testing in pregnancy and regular follow-ups as scheduled in the study (Table 1). Baseline sociodemographic information will be collected from participants who discontinue.

**Table 1 Tab1:** Interventions for the pregnant mothers and its target behavioral correlates

Content of intervention	Operationalized as	Target Behavioral correlate
Mother and Baby Workshop(MBA)	Workshops on healthy diet, GDM, immunization, seminars, token of appreciation and a meal for the parents	Participants turning up for OGTT,follow up at delivery and 3.5 months
Interactive voice response system (IVRS)	IVRS calls to participants for reminding OGTT, follow up visit, child immunization. Regular IVRS call providing health advice to pregnant women and mothers on diet and child care	Participants turning up for OGTT, follow up at delivery and 3.5 months

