### Outcome measures

#### The primary outcome is the proportion of participants visiting the hospital for OGTT before 36 weeks of gestation

OGTT requires overnight fasting of minimum 8–12 h; the pregnant women will have to come early morning to the research hospital after which the fasting venous sample will be drawn. The research staff will administer 82.5 g of glucose (equivalent to 75 g of anhydrous glucose) mixed with 250 ml of water. Blood will be drawn again after 2 h, and the blood sugar level is measured. Successful follow-up assessment means that the pregnant woman has completed OGTT before the end of 36 gestational weeks. The response rate is the number of women completing the OGTT divided by the total number of women who were due for undergoing OGTT within  36 weeks of gestation. The loss to follow up is defined as the number of women who missed OGTT divided by the total number of women who completed 36 weeks of gestation. The eligibe duration for undergoing OGTT is 14 weeks, starting from 22 weeks till the end of 36 gestational weeks.

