### Statistical analysis

Descriptive statistics of participants’ baseline characteristics will be presented to assess their comparability. These statistics will be reported as a mean (SD) or median (first quartile, third quartile) for continuous variables, and count (per cent) for categorical variables. Baseline characteristics will include age, education, occupation, income, parity, gestational age, and mobile phone access. We calculate the response rate for OGTT in each of the study arms. For the primary analysis, we will compare the proportion of participants retained during the eligible period in the MBA and IVRS group with those in the control group using a Chi-square test.

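### The primary Chi-square test is valid but leaves entry gestational age and other collected baseline predictors unused, giving up a small, nearly free gain in precision

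*Protocol article*

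**What the plan says.** The Statistical analysis section sets the primary comparison of proportions "in the MBA and IVRS group with those in the control group using a Chi-square test". No covariate enters it. The same section says "Baseline characteristics will include age, education, occupation, income, parity, gestational age, and mobile phone access" and gives their purpose: "Descriptive statistics of participants’ baseline characteristics will be presented to assess their comparability".

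The Inclusion criteria admit women from 14 to 36 weeks of gestation. On the test window the protocol gives two starting points:

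- Implementation: "They are invited to undergo the OGTT between 24 to 36 weeks of gestation". The Background also uses 24 to 36 weeks.
- Outcome measures: the eligible period runs "starting from 22 weeks till the end of 36 gestational weeks".

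Study design describes a computer-generated 1:1:1 list and mentions no stratification factor. The Background says that selective attrition is higher in, among others, "those with low family income or low education". It also says, of the interval between OGTT and delivery, "The duration without contact increases the likelihood of attrition". Sample size assumes 77% OGTT completion, an improvement of 10 points, 80% power and 5% significance, and ends with 265 women per arm.

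**The concern.** Entry age is tied by design to the opportunity to complete the primary outcome. A woman enrolled at 14 weeks cannot be tested for at least 8 or 10 weeks. One enrolled inside the window has no imposed wait. One enrolled at 35 weeks has about a week left. If completion differs along this range, part of the outcome variance is explained by a value known before allocation, since gestational age is needed to judge eligibility. Education, income, parity and phone access may explain a little more.

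An unadjusted test leaves all of that variance in the error term. The confidence interval is then wider, and power lower, than the same data allow. A chance imbalance in entry age is also not corrected in the estimate. An analysis plan that is not shown could add adjusted analyses, but this text already fixes which test is primary.

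**Working it through.** **Plan's own figure.** Sample size states 50 per arm for the primary outcome, including 30% non-response. The usual two-proportion formula, two-sided 5% and 80% power, with mean proportion 0.82, gives

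n = [1.96·√(2·0.82·0.18) + 0.842·√(0.77·0.23 + 0.87·0.13)]² / 0.10² = 231 per arm before non-response.

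So 50 is not reproduced; power at 50 per arm is about 25%. That is a separate and larger matter. The recruitment target comes from the secondary outcome (104 × 1.5 = 156; 156 × 1.7 = 265.2) and is used below.

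**Unadjusted power at 265 per arm.**

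- SE under the null: √(2·0.82·0.18/265) = 0.03338
- SE under the alternative: √((0.1771 + 0.1131)/265) = 0.03309
- Power = Φ[(0.10 − 1.96·0.03338)/0.03309] = Φ(1.045) = 85.2%. With the unpooled SE throughout: Φ(0.10/0.03309 − 1.96) = 85.6%.

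**Adjusted power.** If baseline values explain a fraction R² of the outcome variance, the effective size per arm is 265/(1 − R²). R² is an assumption; the documents give no figure.

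| R² | Effective n per arm | Power | Gain (points) | SE ratio |
|---|---|---|---|---|
| 0 | 265 | 85.2% | – | 1.00 |
| 0.02 | 270 | 85.9% | 0.7 | 0.99 |
| 0.05 | 279 | 86.9% | 1.7 | 0.975 |
| 0.10 | 294 | 88.7% | 3.5 | 0.949 |
| 0.20 | 331 | 92.0% | 6.8 | 0.894 |

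**Cross-check with entry age alone.** Assume entry age uniform over 14 to 36 weeks and a logistic effect on completion. With p₀ and p₁ the control and intervention probabilities given entry age, the variance of the standardised difference is [E p₀(1−p₀) + E p₁(1−p₁) + Var(p₁−p₀)/2]/n. Unpooled power then moves as follows:

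| Odds ratio per SD | Control completion across entry ages | Variance ratio | Power (from 85.6%) |
|---|---|---|---|
| 1.2 | 71–82% | 0.995 | 85.7% |
| 1.5 | 63–88% | 0.977 | 86.4% |
| 2.0 | 53–93% | 0.938 | 87.7% |
| 3.0 | 40–97% | 0.866 | 90.1% |

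**Non-monotone case.** In 20,000 simulated trials with three entry-age bands (assumed shares 0.45/0.41/0.14), a pooled z test was compared with a Cochran–Mantel–Haenszel test by band:

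- No band effect: 85.9% versus 85.7%, a cost of 0.2 points. This is within the simulation error of a single estimate, √(0.86·0.14/20,000) = 0.25 points.
- Control completion 65/92/72%: 85.5% versus 87.8%, a gain of 2.3.
- Control completion 55/98/80%: 84.2% versus 90.1%, a gain of 5.9.

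**Sensitivity.** If alpha were split to 2.5% for the two comparisons, which the protocol does not state, power would be 77.7% unadjusted and 82.2% at R² 0.10.

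**The case against.** The strongest reply is that nothing here is an error. A Chi-square test on randomised proportions is valid. It matches an outcome defined as a proportion and a sample size planned for two proportions. At 265 per arm it exceeds the plan's 80% target. Adjusted supporting analyses are commonly left to an analysis plan. All of this stands except the last step: the article does fix the unadjusted test as primary, so a better choice of primary test is a comment on what the text says.

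A reader might also infer that the protocol itself names these covariates as drivers of OGTT attendance. It does not. The statement on income and education concerns cohort attrition in general, and the remark on time without contact concerns the period after the OGTT. Both support the point only by analogy. No section links parity, phone access or entry age to OGTT completion. The argument from entry age rests on the eligibility range and the test window alone, and there it sets a minimum wait, not the actual visit date. Since the test needs an overnight fast and an early-morning visit, enrolment inside the window does not mean immediate testing.

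Adjustment also does not cure any dilution from late entrants who have little time to attend a monthly workshop held before the OGTT. That is a matter of exposure, not of precision.

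**Conclusion.** The point holds as a small improvement in efficiency. Under an assumed R² of 0.02 to 0.10, the gain is about 1 to 3.5 power points at 265 per arm, from about 85% to about 86–89%. The price is about 0.2 points if the covariates have no prognostic value, as simulated for a three-band stratified test.

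Three stronger readings are tempting and not supported:

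- **Bias.** Chance imbalance under randomisation is already allowed for in the error rate of the unadjusted test. The protocol mentions no stratification factor that the analysis then ignores; a condensed article's silence does not prove that there is none.
- **Inadequate power because of this choice.** Under the planning assumptions, 265 per arm exceeds the unadjusted requirement of 231.
- **A large gain.** Eight points (85.6% to 93.7%) would need a correlation of 0.5 between baseline values and completion, that is an R² of 0.25. Nothing in the documents supports this. Even a 27-point spread in completion between entry-age bands yields only 2.3 points.

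**What to change.** In the Statistical analysis section, name as primary a logistic model of OGTT completion on arm, entry gestational age and a short list of covariates already collected: education, income, parity, and mobile phone access as recorded. Enter gestational age in bands or another non-linear form, because the relation need not be monotone. Place a cut-point at the start of the OGTT window once the 22-week and 24-week statements have been reconciled.

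Report the standardised difference in proportions for each intervention versus control with its 95% confidence interval, so that the target quantity remains a difference in proportions. Keep the Chi-square test as a supporting analysis. Use the same covariates for the delivery and 3.5-month outcomes.

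The cost is a change of wording and a little more analysis work, with no new data and no further participants. The covariates and bands must be fixed before outcome data are seen, and the result takes slightly more explaining than a Chi-square.

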## Discussion

Earlier evidence suggests that the relationship between the patient and the study personnel is an essential factor in subject accrual and continued participation. E.g., patients who received the nursing interventions based on self-regulation theory experienced less disruption in their usual life activities during and following radiation therapy [29]. Similarly, IVRS too has been gaining acceptance in a variety of studies, ranging from symptom and mood monitoring to adverse event reporting and medication compliance [30]. Additionally, IVRS is used in various populations, including lower socioeconomic profile and difficult-to-reach subjects such as those recovering from drug abuse, economically disadvantaged drinkers with AIDS, and low-income public clinic patients [31, 38, 37]. Study participants using IVRS have reported a high degree of user satisfaction, noting that it is both user-friendly and convenient. However, one real limitation for all IVR systems is that the vast majority of intended users ignore them. Thus, the feasibility of using IVRS on a large scale to address health problems is another critical issue to study [36]. Studies involving counselling and antenatal sessions have been successful in encouraging women to breastfeed [32], increasing energy and protein intake among pregnant women [33] and general antenatal information provision [34, 35].

Studies have to continually innovate and try newer interventions in order to sustain participation. Earlier evidence indicates that use of behavioural intervention was effective in improving health outcomes [11] such as increasing retention in HIV care among pregnant mothers [12], improved contraceptive use [13], to improve medication compliance [14] for the regular follow-up of children and adolescents in psychiatric care [15]. IVRS and telecommunication technology has been effectively used to improve maternal and child health care by providing regular information [16, 17]. Using an intervention to prevent the loss to follow up in a birth cohort is a unique initiative. The validity concerns in cohort studies necessitate this.

## Abbreviations

ANC: Ante-natal checkup
ASHA: Accredited Social Health Activist
AWW: Anganwadi Worker
GDM: Gestational Diabetes Mellitus
HIV: Human Immunodeficiency Virus
IEC: Institutional Ethics Committee
IIPH-H: Indian Institute of Public Health-Hyderabad
IVRS: Interactive voice response system
MAASTHI: Maternal antecedents of adiposity and studying the transgenerational role of hyperglycemia and insulin
MBA: Mother and baby affairs
NFHS: National Family Health Survey
OGTT: Oral Glucose Tolerance Test
RCT: Randomized Controlled Trial
RID: Respondent identification number
SD: Standard deviation
